### Data collection

At each point in time, an average of 3,000 opportunities for hand hygiene in approximately 900 nurses will be observed. We will use direct, but unobtrusive observation because this is considered the gold standard and the most reliable method for assessing compliance rates [1,31-33]. At the beginning of each observation period, nurses will be informed that the observers are conducting research on medication errors and other patient safety issues, but not that hand hygiene will be monitored. Observers will conduct their observations at times with a high density of care, mostly during the morning shifts. Observers will be blinded for the strategies delivered to the wards under observation.

### Observer variability

For each observation period, we will train 10 student nurses, all completing their nursing education and experienced in patient care, as well in collecting data. All student nurses will participate in a two-day training course on understanding the indications for hand hygiene during patient care. They will also learn to apply the observation method and to use the data collection form. Before conducting the observation sessions, the observations by the student nurses will be validated. Visual examples of patient care episodes will be presented, and the students will score related hand hygiene opportunities. Then, we will compare the results of the students and discus discordant notifications. Subsequently, we will undertake parallel monitoring sessions in a non-participating hospital. Every student nurse will perform twenty observations jointly with an experienced observer.

We will use a three-step approach to compare the concordance between the observer and the experienced observer. First, we will calculate the concordance between 'the number of recorded hand hygiene opportunities' of the student nurse and the experienced observer. Then, we will calculate the concordance between 'the number of recorded hand hygiene indications' of both observers. Finally, we will calculate the concordance between 'the number of recorded actions.' The Wilcoxon rank test will be used to detect differences between the student nurses and experienced observer.

### Statistical analysis

The effects of the two strategies will be evaluated on an intention-to-treat basis by comparing the hand hygiene compliance rates in the two study groups after performing the strategies with the compliance rates at the end of the reference period. The differences between the two strategies will be evaluated by comparing the hand hygiene compliance rates of both groups after performing the strategies. Multilevel analysis will be applied to compensate for the clustered nature of the data (compliance is clustered within healthcare workers who are clustered within units) using mixed linear modelling techniques, including the following covariates: ward (random effect), HCW (random effect, nested within ward), institution and the baseline results of the wards. The relevance of nurses' gender, ward specialism, and type of hand hygiene opportunity will also be explored by performing sub group analyses.

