**Methods/design:**

This study is a cluster randomised controlled trial with inpatient wards as the unit of randomisation. Guidelines for hand hygiene will be implemented in this study. Two strategies will be used to improve the adherence to guidelines for hand hygiene. The state-of-the-art strategy is derived from the literature and includes education, reminders, feedback, and targeting adequate products and facilities. The extended strategy also contains activities aimed at influencing social influence in groups and enhancing leadership. The unique contribution of the extended strategy is built upon relevant behavioural science theories. The extended strategy includes all elements of the state-of-the-art strategy supplemented with gaining active commitment and initiative of ward management, modelling by informal leaders at the ward, and setting norms and targets within the team. Data will be collected at four points in time, with six-month intervals. An average of 3,000 opportunities for hand hygiene in approximately 900 nurses will be observed at each time point.

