### Study design

The study will have a stratified cluster randomised trial design. In a cluster randomised trial, groups of individuals rather than individuals are randomised [27]. Cluster randomisation using wards as the unit of allocation reduces contamination between groups [28]. In our study, the quality improvement strategies involved the entire team of nurses and not individual nurses on nursing wards. Therefore, nurses within the same ward were considered to be a cluster.

Data will be collected for a six-month reference period--no strategy for promoting hand hygiene--prior to the trial (T1 and T2). After data collection for this reference period, randomisation to either the state-of-the-art strategy or the extended strategy will take place. Strategies will be delivered during a second period of six months. Follow-up measurements will take place directly after strategy delivery (T3) and at six months after the end of strategy delivery (T4). Because the extended strategy consists of the state-of-the-art strategy supplemented with team-directed social influence approaches, randomisation of wards to each of the strategies is feasible. Our study design is illustrated in figure 1.

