## Discussion

Changes in healthcare can target individual professionals, teams and units, or healthcare organisations [15]. Traditionally, implementation strategies are directed at individual professionals (individual level) or address structural work context (organisational level), whereas team-directed strategies are rarely studied. The unique contribution of the extended strategy was built upon social learning theory, Social influence theory [23], theory on team effectiveness [20,20,25,25,26,26] and leadership theory [24]. Together, these theories provide a coherent set of methods to target the social context in which hand hygiene behaviour takes place. Because targeting social context is not often employed in implementation strategies, the results of our project will considerably add to the general body of knowledge by evaluation of the added value of the extended strategy as compared to the state-of-the-art strategy.

Results from our study will allow us to draw conclusions on the effects of different strategies for the implementation of hand hygiene guidelines, and based on these results we will be able to define a preferred implementation strategy for hospital-based nursing. Our evaluation of the state-of-the-art strategy will validate the effectiveness of this strategy in Dutch hospital care. The evaluation will further provide a longer term follow-up effect estimate, whereas commonly only effects during or directly after strategy delivery are evaluated [15,16].

We believe our study has methodological strengths because of the large numbers of observations and participating wards, the randomisation of wards either to the state-of-the-art strategy or the extended strategy, and the use of unobtrusive observations.

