We anticipate several challenges in conducting this study. First, in an ideal world, one would choose randomisation of wards or teams to three groups: a state-of-the-art strategy group, an extended strategy group, and a no strategy group. However, as the state-of-the-art strategy includes hospital-wide campaign elements (*e.g*., posters on doors, instruction leaflets, and short articles in hospital magazines), three-group randomisation at the level of wards would certainly introduce contamination of the no strategy group. This implies that three-group randomisation in the same hospital is not a feasible option. We will collect baseline data twice, with a six month interval, in order to create a reference period with no strategy. Second, timely and accurate data collection for this study is also challenging. To ensure that comprehensive data collection is feasible in all participating hospitals, we will partner with an established Faculty of Health and Social Studies in recruiting, training, and assessing the students who will perform the observations.

Third, in this study we will not measure nosocomial infections. Measuring nosocomial infections on ward level and correcting for all possible interference from other factors would be labour intensive and costly. Given the fact that the relationship between hand hygiene and the occurrence of infections already is well established, and given practical difficulties in achieving comparable patient groups with regard to risk factor and scoring patients who transfer between wards, we decided to use a model-based estimate of HAIs.

Finally, we will not measure compliance in physicians or other healthcare workers. The main reason for not including physicians is the difference in team structure and teamwork between nurses and physicians. Whereas hospital nurses typically work and interact in ward-based teams, physicians more often work independently and on various locations. Targeting physician-directed social influence would ask for strategies other than targeting nurse-directed social influence. Nevertheless, the state-of-the-art strategy is visible to all hospital staff, and may affect physicians' hand hygiene as well.

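### Each strategy's before-after effect is judged against T2 alone, so the no-strategy change from T1 to T2 enters no stated comparison

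*Protocol article*

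**What the plan says.** The Study design section sets up two measurements before randomisation: "Data will be collected for a six-month reference period--no strategy for promoting hand hygiene--prior to the trial (T1 and T2"). The Discussion gives the reason. Hospital-wide campaign elements would contaminate an untreated group, and "This implies that three-group randomisation in the same hospital is not a feasible option". The substitute follows: "We will collect baseline data twice, with a six month interval, in order to create a reference period with no strategy".

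After randomisation, "Follow-up measurements will take place directly after strategy delivery (T3) and at six months after the end of strategy delivery (T4"). The abstract gives the spacing: "Data will be collected at four points in time, with six-month intervals".

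The Statistical analysis section on hand hygiene compliance describes two comparisons. The effect of each strategy compares compliance "after performing the strategies with the compliance rates at the end of the reference period". The difference between strategies compares the two randomised groups after delivery. The multilevel model includes the wards' baseline results as a covariate, without naming the time point.

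The Discussion then claims: "Our evaluation of the state-of-the-art strategy will validate the effectiveness of this strategy in Dutch hospital care".

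**The concern.** The design builds a stand-in for the missing untreated arm, and the stated comparator leaves it out. Both arms receive the state-of-the-art package, so randomisation gives no information on whether that package works. Any claim about it rests on the change over time within wards. Measured from T2 alone, that change is the strategy effect plus whatever would have happened anyway.

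T2 and T3 are six months apart and so fall in opposite seasons. T2 and T4 are twelve months apart and share a season, but they span a year of drift. Observer training is repeated for each observation period, so a change in scoring between waves is one possible source of drift.

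At stake are the before-after effects, the longer-term effect estimate and the claim to validate the state-of-the-art strategy. The article's single hypothesis, extended versus state-of-the-art, is not at stake.

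**Working it through.** **Inputs from the article.** 30 wards per arm (Setting and participants). 50 observations per ward per time point, 15 nurses per ward, ward-ICC 0.05, nurse-ICC 0.6, expected gain 15 points for the state-of-the-art strategy and 10 more for the extended strategy (Sample size).

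**Assumptions.** Compliance near 50% (the article says only that it is generally below 50%); different nurses at each wave; nurse-ICC read as the total correlation within a nurse; a drift of 5 points; correlation r of ward effects between waves from 0 to 1. The article gives no value for drift or r.

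**The plan's own figure.** Observations per nurse: 50/15 = 3.33. Design effect: 1 + 2.33 × 0.6 + 46.67 × 0.05 = 4.73. For 65% versus 75%, 329 independent observations per arm are needed, so 329 × 4.73/30 = 51.9 per ward. Power at 50 per ward is 0.786. The stated size is reproduced closely at a 50% baseline.

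**What each contrast carries when the strategies do nothing.** Let s be drift per six months and ±a an alternating seasonal swing. The expected values are T1 = a, T2 = s − a, T3 = 2s + a, T4 = 3s − a.

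| Contrast | Bias |
|---|---|
| T3 − T2 | s + 2a |
| T4 − T2 | 2s |
| T3 − T1 | 2s |
| (T3 − T2) − (T2 − T1) | 4a |
| (T4 − T2) − 2(T2 − T1) | 4a |

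With s = 5 and a = 0, T3 − T2 is biased by 5 points and T4 − T2 by 10, against an expected gain of 15.

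**Precision.** In units of p(1−p), the ward-mean variance has a ward part of 0.05 and a sampling part of 0.55/15 + 0.40/50 = 0.0447. For a contrast whose coefficients sum to zero, with sum of squares C, the SE in one arm is √[C × (0.0447 + 0.05(1 − r)) × 0.25/30].

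- T3 − T2: C = 2
- (T3 − T2) − (T2 − T1) = T3 − 2T2 + T1: C = 1 + 4 + 1 = 6
- (T4 − T2) − 2(T2 − T1) = T4 − 3T2 + 2T1: C = 1 + 9 + 4 = 14

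| r | SE of T3 − T2 | Significant under 5-point drift | SE, T3 trend-corrected | Power for 15 points | SE, T4 trend-corrected | Power for 15 points |
|---|---|---|---|---|---|---|
| 1.0 | 2.73 | 45% | 4.73 | 89% | 7.22 | 55% |
| 0.8 | 3.02 | 38% | 5.23 | 82% | 7.99 | 47% |
| 0.5 | 3.41 | 31% | 5.90 | 72% | 9.02 | 38% |
| 0 | 3.97 | 24% | 6.88 | 59% | 10.51 | 30% |

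Example for r = 1: √(2 × 0.0447 × 0.25/30) = 2.73 points; 5/2.73 = 1.83; P(|Z + 1.83| > 1.96) = 0.45. At 40% compliance the range over r is 25% to 46%. A drift of 2 to 3 points gives about 8% to 20%.

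**Baseline covariates in the between-arm model.** The share of variance explained by T2 alone and by T1 with T2 is 0.279 and 0.365 at r = 1.0, and 0.100 and 0.153 at r = 0.6. The remaining variance falls by 1 − 0.635/0.721 = 12% and 1 − 0.847/0.900 = 6%.

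**The case against.** The strongest reply is that the trial's one hypothesis is tested between concurrent randomised groups, where common drift and season cancel, and that the sample size is built around the added 10 points. This stands. A reader might infer that the main comparison is biased; the documents do not support that.

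A reader might also infer that T1 is collected and never used. The article calls both early waves baseline, and the undated baseline covariate may include T1. That stands too, but a ward-level covariate does not estimate the no-strategy change over time, so the gap remains.

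It can be said that a condensed article leaves modelling detail to the full plan. That does not help here, because the comparator is stated rather than left open.

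The obvious remedy also has a cost. Subtracting the T1-to-T2 change removes linear drift but turns a seasonal bias of 2a into 4a. At T4, subtracting it once leaves s + 2a, which adds season to a contrast that had none; removing twelve months of drift requires subtracting it twice, with low power. These points stand, so no single corrected contrast should replace T3 − T2.

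Finally, the Discussion openly explains why there is no untreated group, and the validation claim is one sentence. That limits the weight of the point but does not remove it.

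**Conclusion.** The point holds for the uncontrolled before-after effects, which are secondary to the randomised hypothesis. As stated, the analysis credits secular drift to the strategies at T3 and T4, and seasonal change at T3 only; season cannot bias T4 − T2.

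For an assumed 5-point drift and no strategy effect, T3 − T2 in one arm would be significant about 24% to 45% of the time instead of 5%. A reader might take 45% as the figure, but it requires ward effects that persist fully between waves, and the article gives no wave correlation. The gap in the text is certain; the numbers are illustrations. The claim to validate the state-of-the-art strategy is stronger than this contrast can support.

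**What to change.** - Fit one multilevel model to all four waves.
- Report the T1-to-T2 change with its interval beside T3 − T2 and T4 − T2 in each arm.
- Report as co-equal checks the season-matched T3 − T1, noting that it still carries twelve months of drift, and the linear-trend-corrected contrasts (T3 − T2) − (T2 − T1) and (T4 − T2) − 2(T2 − T1).
- State that the trend-corrected contrasts assume linear drift and no alternating season, and that they are imprecise, above all at T4.
- State that T1 and T2 ward compliance are both baseline covariates in the between-arm model. For wave correlations of 0.6 to 1.0 this cuts its variance by about 6% to 12% compared with T2 alone.
- In the Discussion, describe the state-of-the-art result as an uncontrolled before-after estimate rather than a validation.

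The cost is wider intervals and a softer claim. No new data are needed.

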### Setting and participants

The study will be performed in three hospitals: one university medical centre and two general hospitals. In a fourth (non participating) hospital, we will test the instruments and observer variability. Within the hospitals, all inpatient wards (n = 60), will participate in the study.

After completing baseline measurements of the reference period, wards will be randomly assigned to either the state-of-the-art strategy group (n = 30), or the extended strategy group (n = 30). The randomisation of the wards will be stratified for type of ward to minimize differences in ward characteristics over the strategies. We will randomise surgical wards, internal medicine wards, intensive care units, and paediatric wards.

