### Sample size

The state-of-the-art implementation strategy should be able to improve hand hygiene compliance with 15% in the short term [1]. We assume an added effect of 10% from the team-directed approach. This means that the extended strategy would be clinically relevant if it would result in an improvement of compliance with 25% of all occasions for hand hygiene. Calculating from 80% power, two-sided alpha = 0.05, a ward-ICC of 0.05 and a nurse-ICC of 0.6, in each of the 60 wards in the study an average of 50 observations of occasions for hand hygiene compliance are needed at each point in time, involving 15 nurses per ward.

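### Randomisation is stratified by ward type, but the main model's stated covariates omit it; if ward type predicts compliance beyond ward baseline and institution, the standard error is too large and the test conservative

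*Protocol article*

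**What the plan says.** Protocol article, Setting and participants: "The randomisation of the wards will be stratified for type of ward to minimize differences in ward characteristics over the strategies". The types are then named: "We will randomise surgical wards, internal medicine wards, intensive care units, and paediatric wards". No other stratification factor is mentioned. The trial runs in three hospitals, and "wards will be randomly assigned to either the state-of-the-art strategy group (n = 30), or the extended strategy group (n = 30").

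Protocol article, Statistical analysis (hand hygiene compliance): the mixed linear model has the terms "ward (random effect), HCW (random effect, nested within ward), institution and the baseline results of the wards". The next sentence is the only place where ward type enters the analysis: "The relevance of nurses' gender, ward specialism, and type of hand hygiene opportunity will also be explored by performing sub group analyses".

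Protocol article, Sample size: "Calculating from 80% power, two-sided alpha = 0.05, a ward-ICC of 0.05 and a nurse-ICC of 0.6", leading to 50 observations per ward from 15 nurses at each time point, for an added effect of 10 percentage points.

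**The concern.** When allocation is stratified on a factor that predicts outcome, the arms are balanced on it, so its contribution largely drops out of the true sampling variance of the arm difference. A model that leaves the factor out does not know this. Whatever ward-type variation the other covariates do not absorb stays in the random ward variance and so in the reported standard error. Intervals are then wider, and the test more conservative, than the design warrants.

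The stated reason for stratifying presupposes that ward type matters. The trial is planned at 80% power for a difference between two active strategies, so part of a gain that the design has already paid for may go unused. The subgroup analyses do not repair this, because they do not bring ward type into the main comparison.

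**Working it through.** **Inputs from the article.** Ward-ICC 0.05, nurse-ICC 0.6, 50 observations and 15 nurses per ward (m = 50/15 = 3.33 per nurse), 30 wards per arm, difference 0.10, two-sided alpha 0.05.

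**Assumptions.** The article gives no baseline rate for the sample size, only a general figure below 50%. I take 50%, hence 65% versus 75% after the strategies. The share f of between-ward variance due to ward type is not given either, so it is varied.

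**1. The plan's own figure.** Design effect = 1 + (3.33 − 1)×0.6 + (15 − 1)×3.33×0.05 = 1 + 1.40 + 2.33 = 4.73. Two proportions, 65% versus 75%, need 329 per arm. 329 × 4.73 / 30 = 51.9 observations per ward, against 50 stated; power at 50 is 78.6%. The figure reproduces approximately. It depends on the assumed rates: 45% versus 55% gives 61.8 per ward and 71% power.

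**2. Ward-mean variance (relative to p(1−p)).** 4.73/50 = 0.0947, of which 0.05 lies between wards and 0.0447 within.

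**3. No baseline or institution adjustment (an upper bound).** With mean proportion 0.70:

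- SE reported without ward type = √(2 × 0.21 × 0.0947/30) = 0.0364.
- True SE under stratified allocation = √(2 × 0.21 × (0.0947 − 0.05f)/30).
- Actual type I error = 2×(1 − Φ(1.96 × SE ratio)).

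| f | True SE | Reported/true | Type I error | Power without type | Power with type |
|---|---|---|---|---|---|
| 0 | 0.0364 | 1.00 | 5.0% | 78.4% | 78.4% |
| 0.2 | 0.0344 | 1.06 | 3.8% | 79.7% | 82.8% |
| 0.5 | 0.0312 | 1.17 | 2.2% | 82.0% | 89.3% |

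This is not the planned model, which also contains baseline and institution. If those two halve the ward variance (0.025 remaining) and f is the share of what remains, the ratio falls to 1.04 (f = 0.2) and 1.10 (f = 0.5). Type I error is then 4.2% and 3.1%, and power is 90.1% versus 91.4% and 91.5% versus 94.2%.

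**4. Close to the planned model.** This is a simulated ward-level analysis of covariance on arm, noisy ward baseline and institution, fitted with and without ward type. It uses 60 wards, four strata, 4,000 null and 2,000 alternative runs per setting. Persistence of a ward's level from baseline to follow-up is set at 0.5 (weak) or 0.9 (strong).

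| f, persistence | Mean model SE / empirical SE, type omitted | Type I, omitted | Type I, included | Power, omitted | Power, included |
|---|---|---|---|---|---|
| 0, weak | 0.0359/0.0367 | 5.3% | 5.3% | 76.2% | 76.3% |
| 0, strong | 0.0327/0.0324 | 4.7% | 5.0% | 82.9% | 82.8% |
| 0.2, weak | 0.0359/0.0347 = 1.035 | 4.3% | 5.3% | 78.0% | 81.0% |
| 0.2, strong | 0.0326/0.0320 = 1.019 | 4.6% | 5.0% | 84.4% | 85.4% |
| 0.5, weak | 0.0356/0.0322 = 1.106 | 3.0% | 4.8% | 80.6% | 87.8% |
| 0.5, strong | 0.0325/0.0306 = 1.062 | 3.4% | 4.3% | 86.3% | 88.8% |

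Baseline adjustment absorbs ward type only in part because a ward baseline from 50 observations is noisy: its reliability is 0.05/0.0947 = 0.53 under the plan's ICCs.

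**The case against.** **No evidence that ward type matters beyond baseline.** This stands. No section gives a figure, and at f = 0 there is no loss. A reader might infer from the omission that the standard error is certainly overstated. The documents support only the conditional statement.

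**Baseline and institution already do much of the work.** This stands for the size. A reader might take the unadjusted figures in step 3 (standard error up to 17% too large, type I error down to 2.2%) as the effect on this trial. They describe a model that the article does not plan. At f = 0.2 the simulated type I errors of 4.3% and 4.6% are also close to simulation noise: with 4,000 runs the Monte Carlo standard error is √(0.05×0.95/4000) = 0.34 points. Only f = 0.5 shows the conservatism clearly.

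**The benefit of stratifying is not thrown away.** This stands. Balanced allocation reduces the true variance whether or not ward type is modelled. With weak persistence, power without ward type rises from 76.2% (f = 0) to 78.0% and 80.6%. What is lost is the further gain from a correctly sized standard error.

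**Institution is a legitimate covariate.** This stands. A reader might infer that it was put in place of ward type by mistake, but nothing in the article says so. With three hospitals, adjusting for it is reasonable; it simply does not do the job of ward type.

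**The full model may be in an unseen analysis plan.** This does not remove the point. The article names its covariates, including one that is not given as a stratification factor, and leaves out the one that is. If the analysis plan already contains ward type, only the article's list is incomplete.

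**Conclusion.** The point holds as a conditional loss of efficiency and is not a threat to validity. The stated model leaves out the only named stratification factor. If ward type predicts compliance beyond ward baseline and institution, the standard error of the arm difference is too large and the test conservative, with no bias and no excess of false positives.

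The size is small to moderate over the assumed range of 20% to 50%, using the plan's ICCs, equal ward sizes and an assumed 65% versus 75%. The low end of the 1-to-7-point power loss belongs to a small ward-type share with a persistent baseline, and the high end to a large share with a weak one. The documents do not show where in this range the trial lies. It is best treated as a free improvement.

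**What to change.** Add ward type, coded as the four randomisation strata, as a prespecified fixed effect in the main mixed model. Keep institution and ward baseline compliance, and keep the random effects as stated.

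The cost is 3 degrees of freedom out of 60 wards. Counting intercept, arm, one baseline term and two institution terms, ward-level degrees of freedom go from 55 to 52. Ward type is known at randomisation, so no new data are needed. In the simulation, including it when it had no effect (f = 0) left power unchanged to within 0.1 point. The exploratory subgroup analyses can stay as they are; this point does not bear on them.

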### Ethical and legal aspects

The Medical Ethics Committee of district Arnhem-Nijmegen assessed the study and concluded that our study was deemed exempt from their approval because it did not include collection of data at the level of patients.

The Hawthorne effect is probably the most important bias in hand hygiene observations [1,30,33,41]. Persons who know they are being observed change their behaviour and are significantly more likely to wash or disinfect their hands. Unobtrusive observation diminishes the Hawthorne effect, but raises ethical questions regarding privacy of the observed participants. Therefore, we consulted the ethical committee. They concluded that unobtrusive observation will be permitted under the following conditions: the observation topic, hand hygiene, will be covered by using general patient safety issues as subject of the observation; the observations on the nurses should be collected and processed anonymously; and prior to the observation, the patient has given verbal permission to observe.

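### One mixed model serves both comparisons, and its random effects do not fit the before-after one: standard errors are too small if time points are stacked and ward levels shift between rounds

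*Protocol article*

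**What the plan says.** The Statistical analysis section for hand hygiene compliance sets two comparisons. The first evaluates each strategy by its compliance rates "after performing the strategies with the compliance rates at the end of the reference period", that is, T3 or T4 against T2. The second is the test of the trial hypothesis: "The differences between the two strategies will be evaluated by comparing the hand hygiene compliance rates of both groups after performing the strategies".

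One description of a mixed linear model follows and covers both. Its listed terms are "ward (random effect), HCW (random effect, nested within ward), institution and the baseline results of the wards". The section does not say whether T2 enters as a response, as a covariate, or as both. It lists no ward-by-time term.

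Under Ethical and legal aspects, "the observations on the nurses should be collected and processed anonymously". The article does not say whether a code will link a nurse's observations across rounds.

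**The concern.** The two comparisons need different models, and either reading of the single description leaves the first comparison in difficulty.

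- **T2 and follow-up both as responses.** One ward intercept, constant over time, assumes that the true level of every ward in an arm moves by the same amount between rounds. Any ward-specific shift then goes into the residual and is treated as if it averaged out over the nurses observed. A nurse random effect does not absorb a shift shared by the whole ward, whether or not nurses can be linked.
- **T2 only as a covariate.** The model then conditions on baseline. It estimates a difference between strategies at follow-up, not a change from the reference period.

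The article gives reasons to expect ward-specific shifts. Rounds are six months apart. Observers are trained afresh for each observation period. Teams in the extended arm set their own targets, and exposure will be graded ward by ward.

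The Discussion explains that a no-strategy arm was not feasible. The before-after comparison, with the T1 to T2 reference period behind it, is therefore the only evidence that either strategy works at all. The Discussion relies on it for the effectiveness of the state-of-the-art strategy in Dutch hospitals and for a longer-term estimate.

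**Working it through.** **Inputs from the Sample size section.** "Calculating from 80% power, two-sided alpha = 0.05, a ward-ICC of 0.05 and a nurse-ICC of 0.6"; "an average of 50 observations of occasions for hand hygiene compliance are needed at each point in time, involving 15 nurses per ward". That is 50/15 = 3.33 observations per nurse. There are 30 wards per arm (Setting and participants).

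**Assumptions.**
- Compliance is near 50%, so p(1−p) = 0.25. This scales all the standard errors (SEs) but not their ratios.
- Nurses are not linked across rounds.
- The correlation r of a ward's true level between rounds is not in the article, so I use 1.0 to 0.5.

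**The plan's own figure.** For a 10-point difference at 80% power:
- Product design effect: (1 + 2.33×0.6)(1 + 14×0.05) = 2.4 × 1.7 = 4.08. At 55% v 65%, 376 per arm × 4.08/30 = 51.1 observations per ward. At 60% v 70%, 356 × 4.08/30 = 48.4.
- Three-level design effect: 1 + 2.33×0.6 + 46.67×0.05 = 4.73. At 65% v 75%, 329 × 4.73/30 = 51.9.

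The stated 50 can therefore be reproduced, depending on the unstated baseline rate and on the form of the design effect. The three-level form is used below.

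**Before-after SE within one arm.** In units of p(1−p):
1. Variance of a ward mean: 4.733/50 = 0.0947, of which 0.05 is the ward effect and 0.0447 is sampling.
2. True SE: √{0.25 × [2×0.0447 + 2(1−r)×0.05]/30}.
3. SE from the listed model: the nurse-mean residual variance is 15×0.0447 = 0.67. Pooling over 29 degrees of freedom per ward adds only 15×0.05×(1−r)/29. The SE is √{0.25 × 2 × residual/(15×30)}.
4. Actual type I error of a nominal 5% test: 2[1 − Φ(1.96/ratio)].

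| r | Model SE (points) | True SE (points) | Ratio | Type I error | z for a 15-point gain |
|---|---|---|---|---|---|
| 1.0 | 2.73 | 2.73 | 1.00 | 5.0% | 5.5 |
| 0.9 | 2.73 | 2.88 | 1.05 | 6.3% | 5.2 |
| 0.8 | 2.74 | 3.02 | 1.10 | 7.5% | 5.0 |
| 0.7 | 2.74 | 3.15 | 1.15 | 8.8% | 4.8 |
| 0.5 | 2.75 | 3.41 | 1.24 | 11.3% | 4.4 |

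A simulation of the stacked model (REML on nurse means, 1,500 runs per value of r) gave ratios of 1.12 at r = 0.8 and 1.19 at r = 0.5, with type I error of 7.8% and 9.5%. The last figure is below the closed form by about two Monte Carlo standard errors: √(0.113×0.887/1500) = 0.8 points, against a gap of 1.8.

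**Where it bites.** The listed model would call a gain significant from about 1.96 × 2.74 = 5.4 points. The correct threshold is 1.96 × 3.02 = 5.9 at r = 0.8 and 1.96 × 3.41 = 6.7 at r = 0.5.

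**Between-strategy comparison.** With T3 as response and ward baseline as covariate, empirical SD over model SE was 1.01, 1.01 and 0.99 at r = 1, 0.8 and 0.5, with type I error of 5.9%, 5.9% and 4.8%. For the average strategy effect with T3 and T4 stacked, the ratio was 0.97 to 1.01.

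**Baseline as both comparator and covariate.** At r = 0.8, adding the T2 ward mean to the stacked model changed the SE of the time effect from 2.74 to 2.73. The SE of strategy × time went from 3.87 to 3.86, and the estimates did not change.

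**The case against.** The strongest reply is that the article never states that time points are stacked. Its list of terms also omits time and strategy, without which neither comparison could be run, so it is plainly not a full specification. A condensed article may leave the time structure to a fuller document. The size of the problem rests on a correlation that the article does not give, and at 1.0 the problem disappears. The comparison at issue is not the randomised one, and the planned gain is large: "The state-of-the-art implementation strategy should be able to improve hand hygiene compliance with 15% in the short term".

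Much of this stands. It makes the point conditional and limits its weight. It does not remove it, because the random effects are named and one description is given for both comparisons. Under either reading of T2, that description does not suit the first comparison.

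Three stronger readings are tempting, and the documents do not support them:
- **That one strategy would be declared better than the other too often.** The planned comparison is of post-strategy rates. At a single time point the ward random effect already contains the ward's variation in that round, and baseline adjustment is ordinary analysis of covariance.
- **That a strategy × time contrast is compromised.** It would be in a stacked model of this kind, but the section does not plan that contrast.
- **That using T2 as both comparator and covariate shrinks the standard errors.** The check shows almost no change. It is unclear wording, and the article does not say that both uses occur in one fit.

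**Conclusion.** The point holds in conditional form and is moderate: it should be fixed, but it does not threaten the test of the trial hypothesis. If T2 and follow-up are responses in the listed model, the correct before-after standard error is about 1.05 to 1.24 times the reported one, and nominal 5% type I error is about 6% to 11%, for between-round ward correlations of 0.9 to 0.5. That range is an assumption. The result also takes the plan's intraclass correlations, 15 nurses per ward and 30 wards per arm as given. If T2 is only a covariate, the before-after effect has no model.

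The expected short-term gain is safe, with z of at least 4.4 throughout the range. The exposure is at T4, for which the article assumes no effect size. A sustained gain estimated at between about 5.4 and 5.9 points (r = 0.8), or between 5.4 and 6.7 points (r = 0.5), would be declared significant when it should not be.

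**What to change.** Describe two models in place of one.

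1. **Between strategies.** Keep what the section most naturally means: follow-up compliance as response, ward baseline rate as covariate, institution, random ward, and nurse within ward. Say that baseline adjustment belongs to this model only. If T3 and T4 share a model and separate effects are read from it, add a random ward-by-time effect; the check above covered only the average effect.
2. **Before-after.** Use the time points as responses, with fixed time and strategy × time, random ward, random ward-by-time, and nurse nested in ward-by-time if nurses cannot be linked across rounds. Include no baseline-rate covariate.

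This changes analysis wording only and needs no new data. The cost is somewhat wider before-after confidence intervals, by about 5% to 24% over the assumed range of correlations.
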